## Abstract

**Background:**

Sleep disturbance in adolescents is common, with up to one-third reporting significant symptoms of insomnia. Research with adults has demonstrated that Web-based cognitive behavioral therapy for insomnia (CBTi) can improve both sleep and mental health. However, research with adolescents is lacking, and we know little about whether CBTi would have similar effects on this younger population.

**Objective:**

This paper summarizes the protocol of a study to assess the feasibility of adding supported Web-based CBTi to the usual care of young people aged 14-17 years attending specialist Child and Adolescent Mental Health Services (CAMHS).

**Methods:**

This is an open trial where we will recruit young people (N=50) aged 14-17 years attending specialist CAMHS with primary or comorbid symptoms of insomnia. In addition to their usual care, young people will be provided with Sleepio, a 6-session, Web-based CBTi self-help program for insomnia. Sleepio teaches a range of techniques including sleep hygiene, relaxation training, stimulus control, sleep restriction, and cognitive techniques that participants will be helped to apply through brief, weekly telephone support calls. Questionnaires and interviews will be completed at baseline and postintervention (8-10 weeks) and will assess sleep, symptoms of depression and anxiety, and acceptability of Sleepio and telephone support.

**Results:**

Recruitment started in May 2018 and continued until the end of October 2018.

**Conclusions:**

This study will provide preliminary evidence about whether supported Web-based CBTi is acceptable to young people with mental health problems and about the postintervention effects on sleep and symptoms of anxiety and depression. This information will determine whether a randomized trial to determine the effectiveness of Sleepio should be undertaken.

**International Registered Report Identifier (IRRID):**

DERR1-10.2196/11324

## Introduction

### Insomnia

Poor sleep during adolescence is common, with insomnia, defined as chronic dissatisfaction with sleep quantity or quality, being the most prevalent sleep disorder [1,2]. Insomnia symptoms are reported by one-third of adolescents and up to a quarter fulfill the diagnostic criteria for insomnia, depending on the definition and method of assessment [3,4]. Insomnia symptoms are persistent [2] and are associated with significant mental health problems including depression, anxiety, substance abuse, and suicidal ideation [3,5-7].

### Association Between Insomnia and Mental Health

Research examining the nature of association between adolescent sleep disturbance and mental health is limited and the findings are inconsistent [8]. There is evidence of a bidirectional relationship, where symptoms of insomnia during adolescence both predict and are predicted by depression and depressive symptoms [9-11]. However, overall, there is more evidence to suggest that insomnia symptoms precede the development of anxiety and depression in adolescence more than the reverse [8,12-14]. This suggests that the provision of interventions that directly address insomnia could reduce the risk of developing mental health problems or reduce current symptomatology [12].

### Cognitive Behavioral Therapy for Insomnia

With adults, there is well-established evidence that treating insomnia can improve mental health including depression [15], anxiety [16], and psychotic experiences [17]. Interventions are based on cognitive behavioral therapy for insomnia (CBTi) and typically include a range of techniques including stimulus control, relaxation training, sleep restriction, sleep hygiene, and cognitive techniques to manage worries and intrusive thoughts [18]. Insomnia interventions can be delivered via the internet, with systematic reviews concluding that Web-based CBTi is effective and improves both sleep and mental health [19-21].

### Cognitive Behavioral Therapy for Insomnia for Adolescents

With adolescents, research examining the effect of CBTi on sleep and mental health is promising but very limited [18,22]. An open, uncontrolled pilot study assessing a 5-week CBTi intervention for depressed adolescents with insomnia found postintervention improvements in sleep and mood [23]. Similarly, augmenting depression treatment with CBTi in a randomized controlled trial involving 40 adolescents aged 12-20 years resulted in positive effects on sleep and depression [24]. In a community study, Bruin et al [25] found that CBTi delivered either face-to-face or over the internet to 12-19-year olds with insomnia was similarly effective and resulted in comparable improvements in sleep and psychopathology (anxiety and depression) compared with a waiting list control group. The authors concluded that improvements in psychopathology were attributable to a reduction of insomnia and recommended that further research should be undertaken within clinical settings.

### Study Aim

The aim of this study is to assess the feasibility of adding supported Web-based CBTi to the usual care for young people aged 14-17 years attending specialist Child and Adolescent Mental Health Services (CAMHS).

## Methods

### Study Design

This is a pre-post uncontrolled mixed-methods feasibility study. The study was funded by the Wiltshire Child Mental Health Commissioning Group, and ethical approval was obtained from the South West-Central Bristol Research Ethics Committee (17/SW/0178).

### Setting

The study will be undertaken in CAMHS within the Oxford Health National Health Services Foundation Trust. The Trust serves a wide geographical area that includes Bath and North East Somerset, Swindon, and Wiltshire.

### Participants

Young people will be eligible to participate if they are aged 14-17 years, attending CAMHS with symptoms of insomnia (ie, time asleep/time in bed ≤85%) as either a primary issue or as a comorbidity, motivated to try and improve their sleep, and interested in using Sleepio.

Motivation is assessed by rating each of 3 questions on a 10-point Likert scale from 0 (strongly disagree) to 10 (strongly agree). The questions relate to problem severity (“At present, sleep is a big problem for me”), desire to change (“I want to change my sleep”), and self-efficacy (“I feel I can change my sleep”). For inclusion, each item must be rated ≥5.

Young people will be ineligible to participate if they are presenting with active suicidal ideation, they have been diagnosed with psychosis, there are current safeguarding concerns (ie, the young person has suffered abuse within the last 6 months or is the subject of a safeguarding investigation), or they have a significant developmental disorder (eg, autism) that prevents them from understanding the program.

As this is a feasibility study, any face-to-face intervention or medication that the young person is receiving through CAMHS will not be interrupted. This trial will, therefore, run alongside any treatment as usual.

### Recruitment and Consent

Clinical staff working in CAMHS teams across Bath and North East Somerset, Swindon, and Wiltshire will identify eligible young people. Interested young people and their caregivers will be provided with a project information sheet, and their details will be passed to the research team. A research assistant will contact the young person to discuss the project, obtain written consent, and complete baseline measures. For those under the age of 16, parental consent will also be required. Meetings will take place at the individual’s home, at the University of Bath, via telephone, or at a community venue, depending on participants’ preference.

### Intervention

Sleepio is an established, fully automated, Web-based, self-administered sleep intervention that has been evaluated with adults [17,26,27]. The intervention is free to study participants and consists of 6 sessions, each lasting approximately 20 minutes, which are released each week. The sessions are accessed via a Web browser on a tablet, desktop, or mobile phone. The program is highly interactional, and content is presented via an animated cartoon therapist (The Prof). Participants complete daily mobile app or Web-based sleep diaries throughout the program, with an algorithm personalizing the content to the individual’s needs. Sleepio is based on CBTi and incorporates cognitive, behavioral, and educational components (Figures 1 and 2).

**Figure 1 figure1:**
[figure not shown]
Sleepio's animated therapist, The [name]: Big Health licensed under fair use.

**Figure 2 figure2:**
[figure not shown]
Part of a Sleepio session around debunking myths about sleep. Source: Big Health licensed under fair use.

#### Cognitive Component

##### Paradoxical Intention

Insomnia sufferers often pay too much attention to their sleep and the consequences of sleep loss. Their worries about not being able to fall asleep increase their anxiety and arousal, which has the effect of inhibiting the onset of sleep. Paradoxical intention attempts to disrupt this unhelpful process. The person is encouraged to deliberately stay awake for as long as he or she can, thereby reducing the anxiety associated with attempting to sleep and resulting in an easier onset of sleep.

##### Cognitive Restructuring

People with insomnia tend to have unrealistic expectations and beliefs about sleep and the consequences of not sleeping. They may overestimate how much sleep they need, underestimate how long they have slept, or catastrophize about the consequences of poor sleep. Cognitive restructuring involves challenging these negative and unhelpful sleep beliefs and developing more balanced and helpful ways of thinking.

##### Mindfulness

Before falling asleep, insomnia sufferers report being very aware of their negative and unhelpful thoughts. They may ruminate about the previous night where they failed to sleep or rehearse worries about the future and how bad the next day will be if they do not sleep. Mindfulness techniques can help individuals to focus on the here and now and to acknowledge and accept their thoughts and feelings without engaging with them.

##### Positive Imagery

Sleep creates anxiety for insomnia sufferers, which contributes to their difficulty falling asleep. To counter this negative perception of sleep and the bedroom, individuals are encouraged to create positive images, thereby reducing anticipatory anxiety.

##### Putting the Day to Rest

Insomnia sufferers often complain of a racing mind, where they ruminate about their day and rehearse what they might need to do in the future. To counter this tendency, people are encouraged to make time before bed to reflect on the day and to plan for tomorrow so that they have emptied their minds before bed.

#### Behavioral Component

##### Sleep Restriction

If sleep is limited, there is a tendency to spend more time in bed in order to catch up. However, people with insomnia find it difficult to fall asleep, resulting in them spending more time in bed awake. Sleep restriction limits the amount of time in bed to maximize the proportion of time spent asleep. As sleep improves, the sleep restriction limit is increased.

##### Stimulus Control

This aims to strengthen the association between bed and sleep. Many insomnia sufferers spend a lot of nonsleep time in bed, tossing and turning, reading, watching TV, gaming, etc. Stimulus control involves establishing bed as a place for sleep. Using bed for nonsleep activities is discouraged, and if the person wakes or is unable to sleep after 15 minutes, he or she is encouraged to get up and do something else relaxing before trying again.

##### Relaxation

To help individuals feel more relaxed and ready for sleep, they are taught a range of relaxation exercises they can undertake. These are designed to relax their body by reducing the physiological sensations of stress, thereby preparing individuals for sleep.

#### Educational Component

##### Sleep Hygiene

This provides information about developing a calming nighttime routine and place to sleep. Information is provided about reducing caffeine, blue screen use, and daytime naps; increasing exercise; and making the bedroom warm, dark, quiet, and free from distractions.

##### The Process of Sleep

This helps discover some important information about the duration of normal sleep, the factors that affect both sleep quality and quantity, and the fact that sleep is an involuntary process.

There are four different areas of Sleepio: sleep diary, case file, library, and community. There is also a Sleepio app that can be used to augment the Web version. The app allows users to fill in their sleep diary, view their daily schedule, and access relaxation audio files.

#### Sleep Diary

Users are required to complete a daily Web-based sleep diary that feeds into the underlying algorithms that tailor the Sleepio program content to the individual.

#### Case File

At the very beginning of the program, users are asked to define the goals that they want to achieve with Sleepio. This progress is tracked throughout and can be viewed in individuals’ case files. Here, they can also view their to-do list and daily schedule that The Prof helps them compile throughout the course. The case file also contains tools such as a recommended reading list, a thought checker, and a day planner, and users can download worksheets and audio files.

#### Library

The library contains articles about sleep, which augment the Sleepio sessions.

#### Community

There is a community section within Sleepio where users can post comments and interact with each other. As this section is not moderated and is intended for adults, young people will be instructed not to access this area of the website.

#### Brief Telephone Support

Engagement with Web-based self-help mental health programs is variable and is typically lower than that with guided interventions [18]. Although Sleepio is a self-administered program, maintaining engagement and program compliance with CBTi may be particularly challenging for adolescents [19]. As Sleepio has not previously been used with this age group, we will augment the programs with brief (15 minutes), weekly support telephone calls from a trained Sleepio Assistant. The assistants have an undergraduate university degree in psychology and previous experience of working with children or young people. They have completed the Sleepio program themselves before undertaking a half-day training focusing on how to facilitate the program with young people. The support calls are designed to maintain motivation and engagement and follow a similar process to that used by Luik et al [27]. The calls will be empathic and motivating and will help the young person reflect on how techniques can be applied to their situation. The call will start by reviewing the young person’s sleep diary followed by a discussion about how any new strategies identified in previous Sleepio sessions have been applied. The discussion will then review the current Sleepio session and how and which new skills can be applied to his or her situation. Finally, the young person’s progress toward achieving his or her goals will be discussed, any questions answered, and the time and date of the next call agreed. The telephone calls are specifically restricted to sleep and the Sleepio program, and no other problems will be discussed. The length of each support call will be recorded.

### Study Procedures

The study procedures are summarized in Figure 3.

Once eligible young people have provided consent and completed baseline measures, they will be emailed an individual access code for Sleepio. A Sleepio Assistant will contact each young person to discuss the goals that they wish to achieve at the end of Sleepio and agree times for future support calls. Sessions are released each week.

**Figure 3 figure3:**
[figure not shown]
Study procedure. CAMHS: Child and Adolescent Mental Health Services; RCADS: Revised Child Anxiety and Depression Scale; MFQ: Mood and Feelings Questionnaire; ISI: Insomnia Severity Index; SCI: Sleep Condition Indicator.

The Sleepio Assistants will monitor progress through the Sleepio dashboard, which summarizes when the young person has accessed each session. Reminder emails and telephone calls will be sent if young people are not engaging with their session. When the 6 sessions have been completed, a member of the research team will arrange to meet with the young person and conduct the postuse assessment.

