### Outcome Measures

The following standardized assessments will be completed pre- (baseline) and post-Sleepio completion (8-10 weeks). Although the program consists of 6 weekly sessions, previous research indicates that the majority of participants complete the course within 10 weeks [28]. Our primary outcome is changes in sleep, with secondary outcomes assessing symptoms of depression and anxiety.

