#### Experience of Sleepio

At the postuse assessment, a semistructured interview will be undertaken with young people to gather detailed feedback on their experience of Sleepio. The postuse interview collects both quantitative and qualitative data. Young people rate on a 4-point scale for ease of use, helpfulness, preference over face-to-face meetings, whether sessions were understandable, and if they would recommend Sleepio to a friend. Changes in sleep, mental health, and overall satisfaction are assessed on a 1-10 scale. Qualitative questions assess how, where, and how often Sleepio was accessed; which techniques and sessions were most useful; experience of telephone support; and how the program can be improved.

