### Statistical Analysis

We will present descriptive statistics summarizing the cohort in terms of age, gender, sleep, and anxiety and depressive symptomology. Descriptive statistics will also be used to summarize engagement with Sleepio in terms of the number of sessions completed versus the number of those who dropped out. *t* test analyses of mean scores will be conducted on the total scores for the pre- and postmeasures of sleep (ISI and SCI) and on the total and subscale scores for the pre- and postmeasures of mood (RCADS and MFQ). This will allow exploration of any changes in sleep or psychological functioning following Sleepio use. Postuse semistructured interviews will be analyzed to determine the acceptability of Sleepio among young people. The interviews will be audiorecorded and transcribed. A predefined framework will be derived from the interview schedule and adapted following participant responses for analysis.

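### The post-assessment and acceptability interview are tied to finishing all 6 sessions, so as written those who stop early have neither and the results describe completers only

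*Protocol article*

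**What the plan says.** Study Procedures (text after Figure 3) sets the trigger: "When the 6 sessions have been completed, a member of the research team will arrange to meet with the young person". That meeting is the post-assessment. Outcome Measures repeats the condition and adds a calendar window: the scales "will be completed pre- (baseline) and post-Sleepio completion (8-10 weeks" (the parenthesis closes there). It supports the window by noting that "previous research indicates that the majority of participants complete the course within 10 weeks". The abstract gives the window without the word completion: "Questionnaires and interviews will be completed at baseline and postintervention (8-10 weeks".

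The interview belongs to the same visit. Experience of Sleepio states: "At the postuse assessment, a semistructured interview will be undertaken with young people to gather detailed feedback on their experience of Sleepio". Statistical Analysis then relies on it: "Postuse semistructured interviews will be analyzed to determine the acceptability of Sleepio among young people". The same section plans t tests of pre and post scores on the ISI, SCI, RCADS and MFQ.

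Three other places bear on the point:

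- Usage records the number of sessions each individual completes, with weekly sleep efficiency and quality ratings.
- Statistical Analysis will summarize sessions completed against the number who dropped out.
- Brief Telephone Support expects engagement to vary and to be hard to maintain in adolescents, and Study Procedures plans reminders for those not engaging.

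**The concern.** The Limitations section names acceptability and feasibility as the primary aim, and Outcome Measures names change in sleep as the primary outcome. Both answers come from one visit, and the only stated route to that visit is finishing the program. The young people who give up are especially informative about ease of use, helpfulness and what should be improved, and they never reach the trigger.

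The abstract says the results will determine whether a randomized trial should be undertaken. That decision would rest on participants selected by having persisted. This is a rule for data collection, so a later analysis plan cannot recover scores and interviews that were not obtained.

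The rule also makes the length of follow-up depend on how quickly someone works through the sessions, so time since baseline is mixed up with engagement in the pre-post comparison.

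**Working it through.** The plan has no figure to reproduce: it gives N = 50 and no power calculation, completion rate or SD. The check is mainly a reading of the text, followed by an illustration.

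**Step 1. Follow one participant who stops at session 2.**

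| Data item | Where stated | Available? |
|---|---|---|
| Baseline scales | Study Procedures (before the access code is sent) | Yes |
| Session count, any diary ratings entered | Usage | Yes |
| Counted as a dropout | Statistical Analysis | Yes |
| Post ISI, SCI, RCADS, MFQ | Outcome Measures, Study Procedures | No, trigger not reached |
| Acceptability interview and ratings | Experience of Sleepio | No, same visit |

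The data that survive are not in the planned t tests, and they do not record the participant's view of the program.

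**Step 2. Follow one participant who finishes after week 10.** Under Study Procedures the visit takes place when the sessions are done. Under Outcome Measures and the abstract it belongs at 8-10 weeks. Both cannot be met. The article claims only that a majority finish within 10 weeks, so some later finishers are to be expected.

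**Step 3. Illustrate what completers alone can tell us about all 50.** Assumptions, none from the article: dropout d between 10% and 50%; 80% of completers find Sleepio acceptable; completers' mean change 0.5 SD. The article defines no acceptability percentage, so the 80% stands for any yes/no summary of the ratings.

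Completers n = 50 × (1 − d); acceptable among them k = 0.80 × n. Over all 50, the lowest possible value is k/50 (no one who stopped finds it acceptable) and the highest is (k + 50 − n)/50 (everyone who stopped does). If those who stop do not change at all, mean change over all 50 is 0.5 × n/50.

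| d | n | k | Lowest | Highest | Mean change over all 50 |
|---|---|---|---|---|---|
| 10% | 45 | 36 | 36/50 = 72% | 41/50 = 82% | 0.45 SD |
| 20% | 40 | 32 | 32/50 = 64% | 42/50 = 84% | 0.40 SD |
| 30% | 35 | 28 | 28/50 = 56% | 43/50 = 86% | 0.35 SD |
| 40% | 30 | 24 | 24/50 = 48% | 44/50 = 88% | 0.30 SD |
| 50% | 25 | 20 | 20/50 = 40% | 45/50 = 90% | 0.25 SD |

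The width of the acceptability range equals the dropout rate. The range extends on both sides of 80%, so the arithmetic alone does not fix a direction. The last column depends on the assumption of no change in those who stop.

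**The case against.** The best counter-argument is that the text says when, not only if. It may describe the ordinary path, with the 8-10 week window as a calendar visit for everyone. Figure 3 is not shown, and a condensed article may leave follow-up of those who stop to the full protocol. This earns some caution. But no visible passage gives another route, Outcome Measures itself attaches the window to completion, and dropout is expected. If another route exists, the text still needs to agree with it.

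Four stronger readings are tempting and are not supported:

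- *Those who stop are never measured, and dropout figures will be missing.* Usage and Statistical Analysis show otherwise. What is missing is the post scores and the interview.
- *Slow finishers are lost.* Under the completion trigger they are assessed late. Nothing excludes a late visit.
- *Acceptability is overstated by a known number of points.* The article has 4-point and 1-10 ratings and a framework analysis, with no acceptability percentage, threshold or completion rate. Any such figure is assumed.
- *The t tests will yield a wrong efficacy claim.* The article calls them exploratory and says that efficacy is not the aim.

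**Conclusion.** The point holds as a fault in a stated collection rule. Followed literally, the article yields post scores and interviews from completers only, and it gives two timing rules that diverge for anyone finishing after week 10.

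A favourable tilt is likely, since people who dislike a program tend to leave it, but that is a judgement. Neither size nor direction can be derived from the article. Under the assumed 80% acceptability among completers, the uncertainty about all 50 is 20 percentage points wide at 20% dropout and 40 points wide at 40% dropout. With few dropouts the problem would be small. The conclusion assumes that neither Figure 3 nor the full protocol provides an assessment for those who stop.

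**What to change.** Amend Study Procedures and Outcome Measures so that the post-assessment and interview are due at one pre-fixed time after baseline, inside the stated 8-10 week window, for every consented participant whatever number of sessions was completed. Offer a brief telephone or online version to those who stopped. The article mentions telephone only for the consent and baseline meetings, so its use here should be stated.

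Report acceptability and pre-post change for all participants assessed. State the number enrolled as the denominator, give bounds for those not reached, and show completers separately and labelled as such. Modelling is no substitute for collection: with one pre and one post score, a participant with baseline only adds little, and only if the data are missing at random.

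The Results section says the study closed at the end of October 2018. If collection can no longer change, label the results as completers only and give the bounds.

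The cost is one extra self-report contact for each participant who stops early, and possibly less favourable results. N stays at 50.

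### The acceptability ratings of Sleepio are collected inside an interview with a research team member, which carries an unacknowledged risk of socially desirable answers; they should be self-completed beforehand

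*Protocol article*

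**What the plan says.** Three parts of the protocol article fix how acceptability is measured.

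- **Who and how.** The Study Procedures text after Figure 3 says that, once the six sessions are done, "a member of the research team will arrange to meet with the young person and conduct the postuse assessment".
- **What is collected there.** Experience of Sleepio says: "The postuse interview collects both quantitative and qualitative data". On the rated items it says: "Young people rate on a 4-point scale for ease of use, helpfulness, preference over face-to-face meetings, whether sessions were understandable". A fifth 4-point item asks whether they would recommend Sleepio to a friend. It adds: "Changes in sleep, mental health, and overall satisfaction are assessed on a 1-10 scale". The open questions include "experience of telephone support; and how the program can be improved".
- **What it is for.** Statistical Analysis uses these interviews to judge acceptability. Limitations describes acceptability and feasibility, not efficacy, as the primary aim at this stage. The abstract's Conclusions make acceptability, together with the effects on sleep and mood, the basis for deciding on a randomized trial.

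The article uses three role labels. For enrolment: "A research assistant will contact the young person to discuss the project, obtain written consent, and complete baseline measures". The support consists of "weekly support telephone calls from a trained Sleepio Assistant". The postuse assessment falls to an unspecified research team member. The article does not say whether these roles are held by different people.

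**The concern.** A rating given to an interviewer is open to social desirability. A young person asked in a meeting how helpful a programme was, and whether they would recommend it, may give a kinder score than they would alone on a form. The interviewer belongs to the team that offered the programme, so the plausible direction is towards approval.

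At stake is the evidence on the stated primary aim. If ratings look better than privately held opinion, the decision on a randomized trial rests partly on an inflated view of acceptability, and weaknesses that should be put right before that trial may go unreported.

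A second, lesser issue concerns the support calls. They are meant to build rapport: "The calls will be empathic and motivating and will help the young person reflect on how techniques can be applied to their situation". The same interview asks about the experience of those calls. If the caller were also the interviewer, criticism of the support would be harder to voice. Support was added because Sleepio had not been used with this age group, so candid comment on it is useful.

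**Working it through.** The protocol gives no figure on this point, and none can be derived. The check is a comparison of the relevant sections.

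1. **Are the ratings given to an interviewer or completed alone?** Experience of Sleepio says that the interview itself yields the quantitative data, and Study Procedures has a team member conduct the assessment at a meeting. The collection mode is therefore stated and is not inferred from silence. No private or self-completed form is described for these items.

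2. **Which items are affected?** Five on the 4-point scale (ease of use, helpfulness, preference relative to face-to-face contact, understandability, recommendation) and three on the 1-10 scale (change in sleep, change in mental health, overall satisfaction): 5 + 3 = 8 rated items. None is described as rating the telephone support, which appears only among the qualitative questions.

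3. **Do the items bear on a main aim?** Yes. Statistical Analysis takes acceptability from these interviews, and Limitations names it as part of the primary aim. Outcome Measures calls change in sleep the primary outcome, but that does not alter the role of the ratings in judging acceptability.

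4. **Is the risk acknowledged?** No. Limitations discusses self-reported sleep without actigraphy and the absence of a comparison group. It does not mention interviewer or social-desirability effects.

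5. **Could the interviewer be the caller?** The text neither says so nor rules it out. Research assistant, Sleepio Assistant and research team member are different labels. Study Procedures names the Sleepio Assistants for monitoring and then changes to the broader term for the assessment. That change may suggest a different person but does not settle it.

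6. **How large is the effect?** Not estimable: the documents give no rate of favourable answers, no expected shift and no count of interviewed participants. The only available scale is the planned sample. With 50 young people, one changed answer moves a proportion by 1/50 = 2 percentage points, and by more if fewer are interviewed. This shows how sensitive the summary is; it does not estimate the bias.

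**The case against.** The strongest reply is that feedback collected by an interviewer is an ordinary choice in an uncontrolled mixed-methods feasibility study, and that who interviews whom is a detail a condensed article may leave to the full protocol. The interview also asks how the programme could be improved, which invites criticism. Engagement is measured separately from the dashboard as sessions completed, with dropout reported, and neither depends on what is said to an interviewer. The ISI and SCI are described as self-report, and the trial decision rests on sleep and mood as well as acceptability.

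Much of this stands. It limits the weight of the point, and it makes the interviewer's identity secondary. It does not answer the main issue, because placing the ratings inside the interview is a stated method and a better one is available at almost no cost.

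A reader might go further in four ways that the documents do not support:

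- That the ratings of the support received are affected. No rated item is described as covering the support.
- That the caller conducts the interview. No section gives one person both tasks.
- That the ratings are biased towards approval. Upward is the plausible direction, but neither presence nor size can be shown.
- That the lack of a control arm makes this worse. Controls without Sleepio could not rate its ease of use, helpfulness or clarity, so they would not offset the effect.

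**Conclusion.** The point holds as a design improvement worth making. The eight ratings of Sleepio and its perceived effects are given within an interview led by a research team member, they inform the stated primary aim, and the resulting social-desirability risk is not acknowledged. The size of any effect cannot be estimated from the documents.

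The conclusion rests on reading the Experience of Sleepio section as it stands, with the ratings given during the interview. If the full protocol already has them completed privately, the article's wording needs correcting but the method does not. The possible overlap between caller and interviewer is an open question about missing detail, relevant only to the qualitative account of telephone support. The point does not invalidate the study.

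**What to change.** 1. In Experience of Sleepio, state that the young person self-completes the 4-point and 1-10 ratings, alongside the postintervention ISI, SCI, RCADS and MFQ, on paper or online, before the interview and out of the interviewer's sight. The interview then covers the open questions.
2. In Study Procedures, state that, where the existing team allows, the interview is conducted by someone who made none of that participant's support calls. This lessens the problem for comments on support but does not remove it, since any team member is linked with the study.
3. In Limitations, add the remaining risk of socially desirable answers.

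The cost is a short extra form and slightly less freedom in scheduling interviewers; no extra visit is needed. Whether step 2 can be met with current staff cannot be checked, because team size is not given, hence its conditional wording. The Results section reports that the study closed at the end of October 2018. If the interviews are already complete, what can still be done is to report how the ratings were collected and who interviewed whom, and to state the limitation.
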